## Abstract

**Background:**

Atrial fibrillation (AF) has several detrimental effects on heart failure patients treated with cardiac resynchronization therapy (CRT). These include suboptimal biventricular pacing and the loss of atrioventricular (AV) synchrony. AV node ablation improves biventricular pacing and clinical outcomes in large observational studies. However, restoration of sinus rhythm with AF ablation may have additional benefits.

**Objectives:**

To compare the effects of AV node ablation and AF ablation on echocardiographic and symptomatic outcomes in patients with CRT and suboptimal biventricular pacing.

**Methods:**

RHYTHMIC is a multicenter prospective randomized controlled trial. Seventy patients will be recruited and randomized to each ablation strategy in a 1:1 ratio. Key inclusion criteria include a previous CRT implant (with atrial lead) for dyssynchronous heart failure, and biventricular pacing <95% secondary to AF. Patients with permanent AF will be excluded.

**Results:**

Patients will undergo baseline assessment including transthoracic echocardiography (TTE), device check, blood tests, electrocardiogram (ECG), 6-minute walk test, and symptom questionnaire. They will then undergo either AV node ablation or AF ablation according to their allocated group. Follow-up will occur at 1 week (TTE and ECG) and at 6 months (repeat of baseline investigations). The primary endpoint will be change in left ventricular ejection fraction on TTE.

**Conclusion:**

This is the first randomized controlled trial comparing AV node ablation and AF ablation in patients with CRT. We anticipate it will provide valuable insight into the management of this frequently encountered clinical scenario in a challenging patient cohort.

Key Findings
▪Atrial fibrillation (AF) is associated with poorer response and increased mortality after cardiac resynchronization therapy (CRT) owing to a reduction in biventricular pacing and loss of atrioventricular (AV) synchrony.▪There is evidence supporting the use of AV node ablation in patients with AF and heart failure treated with CRT.▪There is also early evidence from the general heart failure population suggesting a benefit for AF ablation; however, the optimal treatment strategy is unclear.▪The RHYTHMIC study is a randomized controlled trial that will directly compare AF ablation and AV node ablation for heart failure patients with CRT and suboptimal biventricular pacing.

## Introduction

Patients with atrial fibrillation (AF) were largely excluded from the landmark trials of cardiac resynchronization therapy (CRT).^1^ However, up to a third of patients receiving CRT in clinical practice have AF.^2^ Heart failure and AF have a complex synergistic interaction, with each influencing the progression of the other. Elevated left atrial pressures caused by left ventricular (LV) dysfunction induce structural and electrical remodeling, which create the substrate for AF. In turn, AF causes rapid and irregular LV activation and the loss of atrial systole, both of which can reduce cardiac output.^1^ The prevalence of AF increases with heart failure severity^3^ and is associated with poorer outcomes, both in the general heart failure population^4^ and in those with electrical dyssynchrony who receive CRT.^5^^,^^6^ Randomized evidence for the use of CRT in patients with AF is limited. In a substudy of the Resynchronization/Defibrillation for Ambulatory Heart Failure Trial (RAFT), 229 patients with permanent AF and dyssynchronous heart failure were randomized to either CRT-defibrillator or implantable cardioverter-defibrillator (ICD) alone.^7^ There was no significant difference in mortality between the groups, and only a borderline significant trend toward fewer heart failure hospitalizations for those who received CRT. However, it should be noted that only 1 patient received an atrioventricular (AV) node ablation, and satisfactory biventricular pacing (>95%) was achieved in only a third of patients. In a recent meta-analysis of more than 80,000 patients, the presence of AF at implant was associated with a significantly higher mortality rate after CRT.^5^ Current guidelines have a class IIa recommendation for CRT in patients with AF and LV ejection fraction ≤35% who meet CRT criteria, provided a strategy is in place to ensure biventricular capture.^8^^,^^9^

AF has a variety of deleterious effects on the delivery of CRT. Firstly, rapid and irregular activation of the ventricles can reduce the delivery of biventricular pacing. In a large study of more than 30,000 patients, atrial arrhythmias were the most common cause for having a biventricular pacing percentage of less than 95%.^10^ Registry studies have consistently shown that suboptimal biventricular pacing is associated with higher mortality rates after CRT, with even very small decreases in CRT delivery affecting outcomes. Low biventricular pacing percentage has also been associated with lower rates of LV reverse remodeling.^11^ In an observational study of 36,935 CRT patients followed up for a mean of 587 ± 324 days, those with biventricular pacing <95% had a 19% increase in mortality (hazard ratio [HR] 1.19; *P* < .001).^12^ Interestingly, patients with AF who had seemingly high biventricular pacing delivery (>98.5%) had a higher mortality rate than those in sinus rhythm with equivalent pacing percentage. This may be related to the fact that biventricular pacing percentage provided on standard device counters likely underestimates true CRT delivery, owing to the presence of fusion and pseudo-fusion beats.^13^ This highlights that the problem of suboptimal CRT delivery in patients with AF is likely underestimated in clinical practice. Secondly, the loss of atrial systole in patients with AF may also attenuate the benefits of CRT. Atrial systole is thought to contribute up to 20%–30% of cardiac output.^14^ Small observational studies have demonstrated the acute hemodynamic benefits of optimizing AV delays during CRT,^15^, ^16^, ^17^ and a recent mechanistic study of 19 patients undergoing His bundle pacing suggested that the majority of the hemodynamic benefit provided by CRT was attributable to shortening of the AV delay, rather than ventricular resynchronization.^18^ It is therefore likely that patients with persistent or permanent AF fail to benefit from this important aspect of CRT. Thirdly, for patients who receive a CRT-defibrillator, AF is an important cause of inappropriate ICD shocks.^19^, ^20^, ^21^ These can have a significant impact on patient quality of life and burden on healthcare services, and have been independently associated with increased long-term mortality.^19^, ^20^, ^21^

As for any patient with AF, the management strategy for those with CRT is either rate or rhythm control. For patients who fail to achieve adequate control with AV blocking agents such as beta blockers or digoxin, invasive management with an AV node ablation completely eliminates AV conduction and renders the patients dependent on pacing. Although this can often achieve biventricular pacing of close to 100%, the presence of ventricular ectopy or tachycardias can still result in suboptimal CRT delivery. There is strong evidence from large observational studies that AV node ablation is associated with reduced mortality after CRT. The multicenter CERTIFY study^22^ examined mortality outcomes after CRT in 7384 patients, and compared those with AF who were treated medically, those with AF who had an AV node ablation, and those in sinus rhythm. Patients with AF who underwent an AV node ablation had significantly lower mortality compared to those treated medically, and outcomes were comparable to those in sinus rhythm. Although no randomized studies have been performed, these findings are supported by a large meta-analysis of more than 80,000 patients^5^ and are reflected in current European guidelines, where AV node ablation has a class IIa indication in case of incomplete biventricular pacing after CRT.^8^ More recently, the randomized APAF-CRT trial^23^ demonstrated a significant reduction in all-cause mortality with AV node ablation and CRT implantation vs pharmacological rate control for patients with severely symptomatic permanent AF and narrow QRS (<110 ms) and at least 1 heart failure hospitalization in the previous year. Although this is a different patient cohort from those with dyssynchronous heart failure and existing CRT devices, it provides further evidence for the benefits of this ablation approach. AV node ablation has also been shown to significantly reduce the risk of both inappropriate and appropriate shocks in patients with CRT-defibrillators.^24^

Rhythm control may have advantages over rate control for patients with CRT, as atrial systole can be restored. Although rhythm control can be achieved with electrical cardioversion and antiarrhythmic therapy, many antiarrhythmic drugs are contraindicated in patients with LV impairment, and long-term maintenance of sinus rhythm likely requires left atrial ablation. AF ablation is feasible in patients with CRT. In a small observational study by Fink and colleagues,^25^ 38 nonresponders to CRT who had AF underwent pulmonary vein isolation. Significant improvements were observed in biventricular pacing percentage, LV ejection fraction, and New York Heart Association (NYHA) class, and 67% of patients were free from AF at 24 months. Randomized studies of AF ablation in the CRT population are lacking; however, evidence can be inferred from trials in the general heart failure population. In the PABA-CHF study,^26^ 81 patients with AF and LV impairment (ejection fraction <40%) were randomized to either AF ablation or AV node ablation with CRT implantation. Patients in the AF ablation group were found to have superior improvements in LV ejection fraction, 6-minute walk test, and heart failure symptoms. In the CASTLE-AF study,^27^ 398 patients with symptomatic paroxysmal or persistent AF and severe LV impairment were randomized to AF ablation or medical therapy. There was a significant reduction in the primary composite endpoint of death or heart failure hospitalization in the ablation group (HR 0.62; *P* = .007), and 63% of patients were free from AF on device interrogation after 60 months of follow-up. 27.5% of patients in this study had a CRT device, and there was a nonsignificant trend toward a lower primary endpoint in this subgroup (HR 0.54; 95% confidence interval 0.28–1.04). However, questions have been raised about the real-world applicability of the findings, given that only 13% of patients screened for the study met inclusion criteria. No study has yet compared rhythm vs rate control strategies in patients with AF and CRT. The RHYTHMIC study seeks to compare AV node ablation with AF ablation for the management of patients with CRT and suboptimal biventricular pacing secondary to AF. We hypothesize that the restoration of AV synchrony with AF ablation will lead to superior LV reverse remodeling compared to AV node ablation.

## Objectives

The primary research objective is to compare the effects of AV node ablation and AF ablation on echocardiographic and symptomatic outcomes in patients with CRT and suboptimal (<95%) biventricular pacing. The principal hypothesis tested will be that AF ablation is superior to AV node ablation in improving LV ejection fraction (primary endpoint). Secondary endpoints will include changes in LV ejection fraction and LV end-systolic volume at 1 week; and changes in LV end-systolic volume, Minnesota Living with Heart Failure Questionnaire Score, NYHA class, 6-minute walk test, NT-proBNP, AF burden, biventricular pacing percentage, ventricular arrhythmias, and inappropriate ICD shocks at 6 months. Procedural complications will be recorded, and exploratory safety outcome differences will be analyzed.

If there is no overall benefit for AF ablation on intention-to-treat analysis, it is important to determine if this is because restoring sinus rhythm has no benefit over rate control, or if the benefits of AF ablation are diluted by a high rate of recurrence. We will therefore perform a subanalysis comparing the clinical endpoints between patients who underwent AF ablation and are in sinus rhythm at 6 months, vs those who underwent AF ablation and are in AF at 6 months, vs those who underwent AV node ablation. If significant benefits are observed for patients who maintain sinus rhythm after AF ablation, the next research objective will be to determine which baseline factors are most useful to predict the chance of success after AF ablation in this patient cohort. Baseline factors tested will include clinical factors (eg, duration of AF, paroxysmal vs persistent AF, age, comorbidities) and imaging characteristics on echocardiography (eg, LV size, LV function, left atrial size). We will also assess if improvement in LV ejection fraction correlates with a reduction in AF burden.

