### Sample size justification

Previous comparisons between AV node ablation and AF ablation in patients with AF and heart failure (not indicated for CRT) found a -1% change in LV ejection fraction with AV node ablation compared to 8% with AF ablation.^26^ Measurements of changes in ejection fraction in CRT patients receiving AV node ablation or AF ablation have a variability of 7.1%–10.7%,^25^^,^^28^ giving a maximum variability of 11%. Assuming a normal distribution, a group size of 32 for each arm would achieve 90% power to reject the null hypothesis of equal means, with an alpha value of 0.05 to detect the 9% difference in change in LV ejection fraction using a 2-sided independent *t* test. This sample size will also ensure satisfactory 80% statistical power for detection of 7.5% difference in change in LV ejection fraction. To allow for an approximately 10% drop-out rate we will recruit a total of 70 patients.

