If the trial shows no significant difference between the 2 ablation strategies, it will be important to determine if this is because there is no additional benefit for AF ablation over AV node ablation, or if the clinical benefit is diminished by a high rate of AF recurrence. Success rates after AF ablation in randomized studies of heart failure patients vary from 50% to 88%.^30^ Furthermore, an international multicenter registry demonstrated that the presence of heart failure reduces success rates after AF ablation in patients with persistent AF (57.3% vs 75.8%), though the equivalent effect for patients with paroxysmal AF was marginal and not statistically significant (78.7% vs 85.7%).^31^ If patients in the AF ablation arm who maintain sinus rhythm at 6-month follow-up display superior echocardiographic remodeling and symptomatic response compared to the AV node ablation group, this will suggest a potential benefit for AF ablation in a select group of patients who have a low risk of AF recurrence after ablation. This would justify further study with a randomized trial focused on this select patient cohort. A variety of factors are known to affect the risk of recurrence after AF ablation in patients with heart failure, including patient age, duration of AF, comorbidities, and structural and electrical left atrial remodeling.^30^ Subanalyses of the RHYTHMIC study provide additional information on which factors predict outcome after AF ablation in patients with CRT devices. We recognize that patient numbers may limit the statistical power to predict outcomes; however, this study may still provide useful hypothesis-generating data to guide the design of larger trials.

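### After a null intention-to-treat result, comparing AF-ablation patients who hold sinus rhythm with all AV-node-ablation patients is open to selection bias and cannot tell no benefit from diluted benefit

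*Protocol article*

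**What the plan says.** The Objectives section makes this subanalysis the response to an intention-to-treat result without overall benefit. Its stated purpose is to decide between two explanations: sinus rhythm offers nothing over rate control, or AF ablation helps but recurrence dilutes the benefit. The groups, formed at the 6-month visit, are "patients who underwent AF ablation and are in sinus rhythm at 6 months, vs those who underwent AF ablation and are in AF", and those who had AV node ablation. The third group is neither split nor selected.

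The Discussion repeats the trigger ("If the trial shows no significant difference between the 2 ablation strategies, it will be important to determine" which of the two explanations applies) and fixes the reading. If the sinus-rhythm subset does better than the AV node arm, "this will suggest a potential benefit for AF ablation in a select group of patients who have a low risk of AF recurrence", and a further randomized trial in such patients would be justified. The same paragraph says that recurrence depends on age, AF duration, comorbidities and atrial remodeling.

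The Statistical analysis section gives t tests for comparisons between arms. Its regression with adjustment for confounders serves prediction of outcomes and is not linked to the three-group contrast. Under Follow-up, only the AF-ablation arm may have a repeat procedure, and the final visit then moves to 6 months after it.

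**The concern.** Rhythm at 6 months is an outcome of treatment and of the patient. Patients who would hold sinus rhythm exist in both arms, but they can be picked out only in the AF-ablation arm. The contrast therefore sets the patients with the better rhythm outlook from one arm against patients of every outlook in the other, and randomization no longer protects it. If the traits that help a patient keep sinus rhythm also go with better LVEF recovery, the subset looks better even when the two procedures are equivalent.

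That defeats the stated purpose. A sinus-rhythm subset that beats the AV node arm is what dilution by recurrence predicts. It is also what no benefit plus prognostic selection predicts. The repeat-procedure rule adds selection, and a later visit, in one arm only.

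At stake is the choice of a follow-on trial and its population. Two explanations of a null result are also too few, because a trial of this size can miss a real difference through imprecision alone.

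**Working it through.** **The plan's own figure.** The Sample size justification gives "a group size of 32 for each arm would achieve 90% power", "with an alpha value of 0.05", "to detect the 9% difference in change in LV ejection fraction using a 2-sided independent" t test, and for the SD "giving a maximum variability of 11" percent. Then n = 2 × (1.960 + 1.282)² × 11² / 9² = 31.4, so 32 per arm. Power at 32 is 90.5% by the normal approximation and 89.6% by the noncentral t. The figure reproduces, so SD 11 and 32 per arm are used below.

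**Inputs for the selection bias.**
- SD of LVEF change 11 and 32 per arm (Sample size justification).
- Fraction p in sinus rhythm: 57.3% and 78.7%, the heart-failure success rates for persistent and paroxysmal AF in the Discussion. Using them for rhythm at the 6-month visit is an assumption.
- Correlation rho between the latent tendency to hold sinus rhythm and LVEF change: an assumption found nowhere in the documents, taken as 0, 0.2, 0.3 and 0.5.
- True difference between the procedures: zero.

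**Formula.** If the top fraction p of a normal latent tendency is in sinus rhythm, the expected spurious advantage is rho × SD × φ(c) / p, where c is the (1 − p) quantile of the standard normal.
- p = 57.3%: c = −0.184, φ(c) = 0.392, so 11 × 0.392 / 0.573 = 7.53 points per unit of rho.
- p = 78.7%: c = −0.796, φ(c) = 0.291, so 11 × 0.291 / 0.787 = 4.06 points per unit of rho.

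**Error rates.** These come from 40,000 simulated trials per scenario, with a pooled t test of the subset against all 32 AV node patients. The last column keeps only trials with a non-significant intention-to-treat result, which is the plan's trigger.

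| p | rho | Bias (points) | Two-sided rejection, all trials | Rejection favouring AF ablation, given a null primary result |
|---|---|---|---|---|
| 57.3% | 0 | 0 | 5.0% | 1.3% |
| 57.3% | 0.2 | 1.5 | 7.1% | 4.7% |
| 57.3% | 0.3 | 2.3 | 10.2% | 8.1% |
| 57.3% | 0.5 | 3.8 | 20.9% | 19.4% |
| 78.7% | 0 | 0 | 5.0% | 0.9% |
| 78.7% | 0.2 | 0.8 | 5.7% | 2.5% |
| 78.7% | 0.3 | 1.2 | 6.9% | 3.9% |
| 78.7% | 0.5 | 2.0 | 10.4% | 8.0% |

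Given a null primary result, the two-sided rate is about 1.6% to 2.6% at rho 0. At rho 0.3 to 0.5 it is about 4% to 19%, nearly all favouring AF ablation.

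**Why the pattern does not discriminate.** Take p = 57.3% and rho 0.3 with no treatment effect. The sinus-rhythm subset lies 2.26 points above the AV node arm. The AF subset lies 0.573 × 2.26 / 0.427 = 3.03 points below it, a gap of 5.29. Sinus rhythm best, AV node in the middle and recurrent AF worst is the picture that dilution would also give.

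**Imprecision of the primary comparison.** The planned 95% CI half-width is t(62) × SD × √(2/32) = 1.999 × 11 × 0.25 = 5.5 points. For illustration, an observed difference of 5 would have an interval of about −0.5 to 10.5. That is not significant, yet it includes the design difference of 9.

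**The case against.** The wording is hedged. The Objectives call this a subanalysis, the Discussion speaks of a potential benefit and of further randomized study, and it describes the prediction work as hypothesis-generating. A reader might infer that the plan commits to a causal claim. It does not, and the primary test stays intention-to-treat. This stands and limits the weight of the point. It does not remove it: exploratory status excuses imprecision, but not a contrast with a foreseeable tilt that is offered as grounds for a new trial.

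The size rests on an assumed correlation. This also stands: at rho 0 there is no bias. The Discussion ties its listed factors to recurrence and does not say that they predict LVEF change, so a tilt toward AF ablation is probable but not documented. That LVEF recovery itself helps to hold sinus rhythm is possible, but the documents do not say so.

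A reader might also quote false-positive rates of 7% to 21%. Those hold over all trials, whereas the subanalysis is triggered by a null primary result. Given that trigger, the low end (about 4%) is below the nominal 5%. The fair reference is then the 2% to 3% expected with no selection, so inflation remains.

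Part of a sound answer is already planned. Statistical analysis lists subgroups by AF type, AF duration and age, and the Objectives plan to model baseline predictors of ablation success. Neither is tied to the inference in the Discussion. Finally, rules for reading confidence intervals may sit in an analysis plan that is not shown, so their absence is no fault. What can be said is that the two explanations offered in this text are incomplete.

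**Conclusion.** The concern holds for an exploratory step, not for the primary analysis. The contrast is open to selection bias, probably in favour of AF ablation, and cannot do the job that the Objectives give it. With no treatment effect, SD 11, 32 per arm and 57% to 79% in sinus rhythm, the bias is 0 points at rho 0, 0.8 to 1.5 at rho 0.2, and 1.2 to 3.8 at rho 0.3 to 0.5. Once the primary result is null, two-sided rejection is about 4% to 19% at rho 0.3 to 0.5, against about 2% to 3% at rho 0. The direction of the problem follows from the design together with the protocol's own list of recurrence factors. Its size is conditional on rho. The documents do not support the stronger reading that the trial is set up to declare AF ablation effective.

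**What to change.** - Keep the three-group comparison, labelled descriptive and non-causal.
- Base the inference in the Discussion on the randomized arm difference in LVEF change across baseline-defined recurrence risk, defined identically in both arms. Either test arm-by-factor interactions for factors already listed (AF type, AF duration, left atrial size) or use one simple risk score fixed in advance. A data-driven score is not advisable: 32 patients at these rates give only about 32 × 0.213 = 7 to 32 × 0.427 = 14 recurrences.
- Report these estimates with confidence intervals as hypothesis-generating.
- In the Objectives and Discussion, add imprecision as a third possible explanation of a non-significant result, with the planned half-width of about 5.5 points.

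The cost is wording and modest analysis on data already collected. The downside is precision. With a two-level factor split evenly (16 per cell, an assumption), the interaction has SE 11 × √(4/16) = 5.5 points. That is twice the SE of the overall difference, 11 × √(2/32) = 2.75. The estimate will be wide and must be presented so.
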